#### In-shoe heel lifts (heel lift group)

Participants randomised to the heel lift group will receive Clearly Adjustable® (Algeos Australia) 12 mm in-shoe heel lifts for both feet. The heel lifts are made of firm multi-layered clear vinyl. Three sizes will be available (small, medium and large) and will be issued according the participants’ shoe size. The Clearly Adjustable® in-shoe heel lifts will have a 3.2 mm PPT® Ultralux top cover applied (Fig. 3) to the upper surface to maximise comfort. Three sets of heel lifts will be dispensed to participants to be worn in up to three of their most frequently worn shoes. Participants will be advised to remove any existing ‘insoles’ from their shoes and to wear the heel lifts as much as possible whilst wearing shoes. The maximum heel lift height (12 mm) will be used, however the height of the heel lifts will be reduced if required (and documented) to fit in the participants’ shoes without causing heel slippage during gait. A handout providing instructions about using the heel lifts will be provided to participants.

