**Fig. 4 Fig4:**
[figure not shown]
Calf muscle eccentric exercise program. Figures **a** and **b** show (**a**) the start position and (**b**) end position of the straight-knee exercise. Figures **c** and **d** show (**c**) the start position and (**d**) end position of the bent-knee exercise. Note the use of a block to aid the contralateral leg in lifting the patient

Initially, resistance will consist of bodyweight, and the participants will stand with all their bodyweight on the injured leg. Once participants can perform both exercises with no pain or discomfort on the injured side, they will increase the resistance component of the program. Participants will be asked to use a weighted back-pack to increase resistance. Participants will begin by adding 5 kg of mass (e.g. bags of sand, books) to the backpack and then perform both exercises (3 sets of 15 repetitions) twice daily. Participants will be advised to increase the load by 5 kg increments.

All participants will be advised that muscle soreness within the first two weeks is to be expected. Participants will be advised to continue the exercise program even if pain presents, however if at any point the pain becomes disabling during the exercise program participants will be advised to stop. Participants will also be advised to apply ice over and around the Achilles tendon for 15 min following completion of each exercise session.

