### Adverse events

Adverse events will be assessed at 2, 6 and 12 weeks via a questionnaire. Participants will be asked if they have experienced any new pain or injuries (ache, discomfort or stiffness) in the past 2, 4 or 6 weeks that has lasted for one day or longer. Participants will be asked to describe the location (region and side), severity (mild, moderate or severe) and duration (days, weeks) of symptoms [66]. If participants experience severe symptoms they will be asked to contact one of the investigators. All adverse events will be included in the final manuscript.

The summary of the data collection time points for each outcome measure is shown in Fig. 5.

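### The adverse-event question covers only new pain or injury, so aggravation of the Achilles tendon is not solicited as a harm and expected soreness has no category of its own

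*Protocol article*

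**What the plan says.** The Adverse events section of the Protocol article fixes how harms are collected: "Adverse events will be assessed at 2, 6 and 12 weeks via a questionnaire". The content is "any new pain or injuries (ache, discomfort or stiffness", and a symptom counts if it is one "that has lasted for one day or longer". The recall periods are 2, 4 and 6 weeks. The details recorded are these: "Participants will be asked to describe the location (region and side), severity (mild, moderate or severe) and duration (days, weeks) of symptoms". No item on cause or expectedness is described. The section then promises: "All adverse events will be included in the final manuscript".

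The section on calf muscle eccentric exercise states: "All participants will be advised that muscle soreness within the first two weeks is to be expected". It also tells participants to carry on through pain but foresees pain that becomes disabling. The heel lift section provides for reducing and documenting the lift height so that it fits "without causing heel slippage during gait".

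Data monitoring states that there is no data monitoring committee. A Trial Management Committee reviews safety reports every two weeks.

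**The concern.** The promise to report all adverse events is only as wide as the question that feeds it. That question turns on the word new. By the inclusion criteria, every participant already has Achilles pain. A flare of that pain, which is the harm most directly tied to loading or offloading the tendon, therefore does not fit the question as worded. Problems that involve neither pain nor injury are not asked about either.

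Ordinary training soreness, by contrast, fits the question well. It is a new ache, and the article expects it in exactly the period that the week-2 questionnaire covers. The same table could then count mild expected soreness and leave out aggravation of the treated tendon. Readers comparing the share of participants with any event might take the result as a safety advantage for heel lifts. These reports are also what the management committee would be looking at.

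**Working it through.** **1. Which events the question takes in.** The wording in Adverse events is set against the rest of the article.

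| Event | Within the question as worded? | Recorded elsewhere? |
|---|---|---|
| Calf soreness of a day or more in weeks 1–2 | Yes, as new ache or stiffness | No separate category described |
| Flare of existing Achilles pain that settles before week 12 | No, not new | VAS and PGIC at 2 and 6 weeks; co-intervention questionnaire if treatment was sought |
| Achilles worse at week 12 | No, not new | VISA-A, VAS and PGIC |
| Blister, rubbing or injurious fall | Arguably, as injury or discomfort | Unsolicited contact with researchers |
| Slipping, or a trip without lasting pain | No | Lift-height reductions documented; unsolicited contact |

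**2. How far the other measures fill the gap.**
- The PGIC has three worse categories, for pain and for function separately. The planned analysis counts only the top two improvement categories as success, so the three worse categories are merged with no change and minimally improved.
- The VAS asks about the worst pain of the past week, while the adverse-event recall periods are 2, 4 and 6 weeks. A flare that settled more than a week before an assessment can escape it.
- Outcome measures places the VISA-A at baseline and 12 weeks.
- Statistical analysis makes the between-group comparisons at 12 weeks, so a flare that has resolved by then would not show in them.

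The data on worsening are thus largely collected, but none of these measures is said to feed the adverse-event report.

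**3. Group size.** The adverse-event section states no figure. The only design figure used here is 46 per group. With a difference of 10, SD 16.9, power 80% and alpha 0.05 (taken as two-sided), the exact t-test needs 45.8, so 46 per group and 92 in all. The stated size is reproduced.

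**4. Illustration of the lean.** Both rates below are assumptions. Let b be the share in each group reporting some other new pain, and s the share of the exercise group with soreness of a day or more, independent of b and absent from the heel lift group. Then:

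exercise share = 1 − (1 − b)(1 − s), and gap = (1 − b)s.

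| b | s | Exercise share | Gap (points) | Gap × 46 participants |
|---|---|---|---|---|
| 10% | 10% | 19% | 9 | about 4 |
| 10% | 30% | 37% | 27 | about 12 |
| 10% | 50% | 55% | 45 | about 21 |
| 20% | 10% | 28% | 8 | about 4 |
| 20% | 30% | 44% | 24 | about 11 |
| 20% | 50% | 60% | 40 | about 18 |

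For example, with b = 10% and s = 30%: 1 − 0.90 × 0.70 = 0.37, and 0.37 − 0.10 = 0.27. Any new ache that heel lifts cause would narrow the gap.

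**The case against.** The strongest reply is that this judges a form nobody can see. The article condenses a fuller protocol, the questionnaire is not reproduced, and it may hold open fields. That lowers confidence. Still, the article does not leave the content of the question open: it states what is asked and what duration qualifies.

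Three stronger readings are tempting, and the documents do not support them.

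- *That harms in the two groups cannot be compared.* Both groups get the same question, time points and duration threshold. Soreness that one treatment causes more often is a real difference in tolerability, and being expected does not stop an event from being adverse. Location, severity and duration would help to identify it. The fault is the lack of a separate category, not that soreness is counted.
- *That the trial misses worsening Achilles pain and device problems altogether.* Worsening is measured in both groups, severe symptoms prompt contact with an investigator, and participants may contact researchers at any time. Lift-height reductions are documented, and injury and discomfort can cover some device problems. Heel slippage is the only such problem the article names.
- *That the promise to report all events contradicts the question.* It can fairly be read as a promise to report what is recorded. The table would simply be narrower than a reader would assume.

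It also stands that adverse events are not a listed outcome and no between-group test of them is named, so no specified analysis is biased. A form changed during recruitment would treat early and late participants differently, which bears on the fix.

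**Conclusion.** The point holds in limited form, as a cheap improvement. Followed as described, the question does not solicit aggravation of the existing Achilles pain, or problems without pain or injury, as adverse events. Expected early soreness enters the count undistinguished. A crude any-event count may therefore lean against exercise and under-record aggravation of the treated tendon.

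The size cannot be drawn from the documents. Under the assumed rates above, the gap from soreness alone runs from 8 to 45 percentage points. The conclusion assumes that the questionnaire matches its description in the article and that some soreness lasts a day or more. The primary analysis is unaffected.

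**What to change.** Collection, on the existing 2-, 6- and 12-week questionnaire:
- Add one item on worsening of the Achilles pain since the last assessment.
- Add one open item on any other problem the participant attributes to the intervention.

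Reporting:
- Tabulate muscle soreness of the first two weeks separately from other events, in both groups.
- Report by group the numbers in each PGIC worse category at 2, 6 and 12 weeks, beside the dichotomised result.

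The cost is a slightly longer form, one coding category and more events listed. Recruitment began in August 2017, so a change to the form may come too late to apply evenly. In that case leave the form alone and make only the two reporting changes, which use data already collected. Treatment, visits and sample size stay as they are.

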**Fig. 5 Fig5:**
[figure not shown]
Data collection time points

### Sample size

The sample size has been determined a priori using the t-test for two independent groups with common variance function in SPSS Sample Power 3.0 (IBM Corporation, USA) based on the VISA–A questionnaire as the primary outcome. Using an allocation ratio of 1:1, a power of 80%, minimal important difference (MID) of 10 points [28], standard deviation of 16.9 [25] (standardised effect size = 0.59) and alpha set at 0.05, we estimate that a minimum of 92 participants (i.e. approximately 46 per group) will be required. We did not allow for participant loss to follow-up in our calculation as missing data will be imputed [67]. Further, we have conservatively ignored the extra precision provided by covariate analysis when estimating the sample size.

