### Statistical analysis

The most recent version of SPSS (IBM Corp., Armonk, NY, USA) will be used to perform statistical analysis. The intention-to-treat principle will be used for all randomised participants. Where participants have bilateral symptoms, the more painful side will be analysed (or the right side if they cannot define the more painful side) to maintain independence of data. Multiple imputation will be used to replace any missing data using five iterations, with sex, age, baseline scores, and group allocation as predictors [67]. However, data substitution will not be applied for the following variables; self-reported magnitude of symptom change, use of co-interventions, adherence and adverse events. Standard tests to assess continuous data for normal distribution (such as assessing skewness and kurtosis) will be used and transformation carried out if required.

The primary outcome measure will be the VISA–A questionnaire measured at 12 weeks. To avoid over-testing and to minimise the risk of type I error associated with serial measurements, statistical analysis of the efficacy of the interventions will specifically focus on the change in primary outcome measures between baseline and 12 weeks [70, 71], and differences in the primary and secondary outcome measures between the two groups will be compared at 12 weeks. To minimise regression to the mean, continuously-scored outcome measures will be analysed using analysis of covariance (ANCOVA) with baseline scores, and intervention group entered as independent variables [72]. Relative risk, risk difference, and number needed to treat (NNT) will be used to compare dichotomous-scaled outcome measures. To complement point estimates, 95% confidence intervals and *p*-values will be calculated where appropriate.

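### Imputation is given as the reason for allowing no loss to follow-up, but it does not restore lost information: on the stated t-test basis, 92 participants give 80% power only if every 12-week VISA-A score is observed.

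*Protocol article*

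**What the plan says.** The Sample size section of the protocol article sizes the trial "using the t-test for two independent groups with common variance function in SPSS Sample Power 3.0". The inputs are a "minimal important difference (MID) of 10 points", a "standard deviation of 16.9", 80% power, "alpha set at 0.05" and equal allocation. The result is 92 participants, about 46 per group.

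Two sentences follow. The first concerns attrition: "We did not allow for participant loss to follow-up in our calculation as missing data will be imputed". The second adds that "we have conservatively ignored the extra precision provided by covariate analysis when estimating the sample size". No expected loss rate and no baseline to 12-week correlation are given.

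The Statistical analysis section specifies multiple imputation with five iterations, "with sex, age, baseline scores, and group allocation as predictors". The primary comparison is an ANCOVA of the 12-week VISA-A on baseline score and group. The Outcome measures section has the VISA-A collected at baseline and 12 weeks. No measurement taken after baseline is listed as an imputation predictor.

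**The concern.** The attrition sentence treats an imputed outcome as equivalent, for power, to an observed one. Properly done, multiple imputation does the opposite: the spread between imputed data sets enters the standard error, so that the standard error reflects only what was observed. Imputation can recover information about a missing outcome only through predictors that the analysis model does not already use. Here the imputation model shares baseline score and group with the ANCOVA, which leaves only sex, age and any other baseline scores. The protocol gives no reason to expect these to explain much of the 12-week VISA-A once its baseline value is known.

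The 80% figure is what justifies recruiting 92 people. If the reason for ignoring attrition is invalid, a reader cannot tell from the protocol what power the trial has once some participants are lost.

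**Working it through.** **Inputs from the Sample size section.** Difference 10, SD 16.9, alpha 0.05, power 80%, ratio 1:1. The section does not say whether alpha is one- or two-sided. Two-sided reproduces 92; one-sided would need only 36 per group (normal approximation), so two-sided is used.

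**Assumed here, not in the documents.** Loss rates of 5% to 20%, equal in both groups, and values of the baseline to 12-week correlation r.

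**Step 1: reproduce the stated figure.** Standardised effect = 10/16.9 = 0.592, matching the stated 0.59. The noncentral-t solution is 45.8 per group, which rounds up to 46, or 92 in total. Power at 46 per group is 80.2%. At 45 per group it is already 79.3%, so there is no reserve.

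**Step 2: t-test power with 92 randomised and a fraction L lost.** Observed n per group = 46(1 − L). Noncentrality = 0.592 × √(n/2), on 2n − 2 degrees of freedom.

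| Assumed loss | Observed n per group | Power |
|---|---|---|
| 0% | 46 | 80.2% |
| 5% | 43.7 | 78.1% |
| 10% | 41.4 | 75.8% |
| 15% | 39.1 | 73.3% |
| 20% | 36.8 | 70.7% |

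**Step 3: the possible offset from ANCOVA, complete cases.** The SD becomes 16.9 × √(1 − r²), with one fewer degree of freedom. Solving for 80% power gives, to a close approximation, r² equal to the loss fraction.

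| Assumed loss | r needed for 80% | Power if r = 0.3 | Power if r = 0.5 |
|---|---|---|---|
| 5% | 0.22 | 81.8% | 88.4% |
| 10% | 0.31 | 79.6% | 86.7% |
| 15% | 0.39 | 77.3% | 84.7% |
| 20% | 0.45 | 74.7% | 82.4% |

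**Step 4: does the planned imputation recover the loss?** Simulation with 92 participants, true difference 10, SD 16.9, outcomes missing completely at random, five imputations (the reading taken of five iterations), results pooled by Rubin's rules with small-sample degrees of freedom, and 4,000 runs. The simulated imputation model held baseline score and group; sex and age were left out, which amounts to assuming that they add nothing. The Monte Carlo standard error is about √(0.75 × 0.25/4000) = 0.7 percentage points.

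| r | Loss | Complete-case ANCOVA | Five imputations |
|---|---|---|---|
| 0 | 10% | 75.0% | 73.6% |
| 0 | 20% | 71.2% | 66.4% |
| 0.3 | 10% | 79.3% | 77.8% |
| 0.3 | 20% | 72.8% | 70.1% |
| 0.5 | 10% | 85.7% | 84.7% |
| 0.5 | 20% | 81.8% | 78.3% |

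Imputation did not raise power above complete-case ANCOVA in any setting. Across repeated simulations at r = 0.5, the five-imputation analysis gave about 84–86% at 10% loss and 77–79% at 20%. The complete-case values of 87% and 82% in Step 3 are therefore not the power of the analysis as planned.

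**The case against.** The strongest reply is that the planned analysis is not the t-test. It is an ANCOVA, and the sentence straight after the one on attrition says that its extra precision was left out of the calculation. A modest correlation covers a modest loss: at 5% loss, r = 0.3 already gives 81.8%. Follow-up lasts only 12 weeks, and the Data monitoring section has a committee reviewing retention every two weeks, so loss may be small. The covariate sentence could also be read as a second reason for leaving the number at 92.

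Much of this stands, and it limits the point. A reader might infer that the trial is underpowered, or that 80% is out of reach once anyone is lost. The documents support neither: they give no loss rate and no correlation, and the statement about complete follow-up applies to the unadjusted t-test, not to the ANCOVA. What does not stand is the imputation rationale. It is the only explicit reason for the zero allowance, and it is wrong whatever r turns out to be. The covariate sentence is introduced as a further remark, with no figure that would let anyone check whether it covers the loss.

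A reader might also infer from Step 4 that imputation itself damages power. It does not. With 50 imputations at r = 0.4 and 20% missing, power was 77–78%, against 78% for complete cases. The extra cost comes from using only five imputations, which is separate from the sample-size rationale.

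**Conclusion.** The point holds in a limited form. The figure of 92 is arithmetically right; the reason for making no attrition allowance is not. On the stated t-test basis, the shortfall against 80.2% is about 2 percentage points at 5% loss (80.2 − 78.1) and about 9.5 at 20% (80.2 − 70.7). These sizes rest on assumed loss rates that are equal in the two groups. The ANCOVA may remove the shortfall wholly or in part, depending on a correlation that the protocol does not state. Type I error and the choice of analysis are unaffected. This should be corrected, but it does not threaten the validity of the trial, and it does not settle whether more participants are or are not needed.

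**What to change.** In the Sample size section:

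- Delete imputation as the reason for making no attrition allowance.
- State that 80% power applies to complete 12-week follow-up without covariate adjustment.
- Give power for 92 randomised at stated assumed losses, for example 78%, 76%, 73% and 71% at 5%, 10%, 15% and 20%.
- If the covariate gain is relied on, state the assumed baseline to 12-week correlation, with its source, and report power for the analysis as planned. With five imputations and r = 0.5, that is about 84–86% at 10% loss and 77–79% at 20%. Do not quote complete-case values for it.

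The cost is one paragraph of wording and a slightly less favourable power statement. The Discussion says that recruitment began in August 2017, so the practical change is to restate the figure. The number randomised and the analysis stay as they are.

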### Statistical analysis

The most recent version of SPSS (IBM Corp., Armonk, NY, USA) will be used to perform statistical analysis. The intention-to-treat principle will be used for all randomised participants. Where participants have bilateral symptoms, the more painful side will be analysed (or the right side if they cannot define the more painful side) to maintain independence of data. Multiple imputation will be used to replace any missing data using five iterations, with sex, age, baseline scores, and group allocation as predictors [67]. However, data substitution will not be applied for the following variables; self-reported magnitude of symptom change, use of co-interventions, adherence and adverse events. Standard tests to assess continuous data for normal distribution (such as assessing skewness and kurtosis) will be used and transformation carried out if required.

The primary outcome measure will be the VISA–A questionnaire measured at 12 weeks. To avoid over-testing and to minimise the risk of type I error associated with serial measurements, statistical analysis of the efficacy of the interventions will specifically focus on the change in primary outcome measures between baseline and 12 weeks [70, 71], and differences in the primary and secondary outcome measures between the two groups will be compared at 12 weeks. To minimise regression to the mean, continuously-scored outcome measures will be analysed using analysis of covariance (ANCOVA) with baseline scores, and intervention group entered as independent variables [72]. Relative risk, risk difference, and number needed to treat (NNT) will be used to compare dichotomous-scaled outcome measures. To complement point estimates, 95% confidence intervals and *p*-values will be calculated where appropriate.

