**Methods:**

Ninety-two participants with Achilles tendinopathy will be randomised to one of two groups: (i) a heel lift group that will receive pre-fabricated 12 mm in-shoe heel lifts (Clearly Adjustable®), or (ii) an exercise group that will be advised to carry out a calf muscle eccentric exercise program (twice a day, 7 days a week, for 12 weeks). Outcome measures will be obtained at baseline, 2, 6 and 12 weeks; the primary endpoint for assessing efficacy being 12 weeks. The primary outcome measure will be the total score of the Victorian Institute of Sport Assessment – Achilles (VISA–A) questionnaire. Secondary outcome measures will include thickness and integrity of the Achilles tendon (using ultrasound tissue characterisation [UTC]), participant perception of treatment effect on pain and function (using the 7-point Patient Global Impression of Change scale), severity of pain at the Achilles tendon (using a 100 mm visual analogue scale) in the previous week, health status (using the EuroQol-5D-5L™ questionnaire), physical activity levels (using the 7-day Recall Physical Activity Questionnaire) and calf muscle function (using the standing heel rise test). Data will be analysed using the intention to treat principle.

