### Outcome measures

The primary outcome will be measured at baseline (prior to randomisation) and at 12 weeks (the primary end-point). All secondary outcomes unless stated otherwise will be measured at baseline (prior to randomisation) and at 2, 6 and 12 weeks (primary end-point). Participants will be encouraged to contact the researchers at any time during the trial.

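### The imputation model leaves out all week 2 and week 6 data, so it adds almost nothing to a complete-case analysis and cannot correct for loss that depends on early response and differs by arm

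*Protocol article*

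**What the plan says.** The Statistical analysis section of the protocol article specifies: "Multiple imputation will be used to replace any missing data using five iterations, with sex, age, baseline scores, and group allocation as predictors". It then says that "data substitution will not be applied for the following variables; self-reported magnitude of symptom change, use of co-interventions, adherence and adverse events". The primary analysis is an ANCOVA of the 12-week score on baseline score and group.

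Under Outcome measures the article says: "All secondary outcomes unless stated otherwise will be measured at baseline (prior to randomisation) and at 2, 6 and 12 weeks". This covers pain VAS, PGIC, EQ-5D-5L and 7-day activity. Ultrasound and the heel rise test are exceptions, taken at baseline and 12 weeks only. Adherence and co-interventions are also recorded at weeks 2 and 6. For the VISA-A the same section gives baseline and week 12 only.

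The Sample size section makes no provision for loss to follow-up, on the ground that missing values will be imputed.

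**The concern.** Imputation helps when it uses information that the analysis model lacks. Here the listed predictors are the two ANCOVA covariates plus sex and age. A participant who responds badly by week 6 and then leaves is given a 12-week score typical of completers in the same arm with similar baseline values. The data that mark this person as a poor responder have been collected but are not used.

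This matters because the design relies on imputation in place of a dropout allowance. Loss that differs by arm is also plausible. The Background and Discussion call the exercise programme time consuming and demanding, with variable adherence, and the Design section says that participants are not blinded.

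**Working it through.** **1. The plan's own figure.** Inputs from the Sample size section: difference 10, SD 16.9, 80% power, alpha 0.05 (two-sided assumed), 1:1 allocation. The standardised effect is 10/16.9 = 0.59. The noncentral t calculation gives 45.8, rounded up to 46 per arm, so 92 in total with power 80.2%. The figure reproduces. With completers only, power of the same t-test at 5, 10, 15 and 20% loss is 78.1, 75.8, 73.3 and 70.7%.

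**2. Bias with a true difference of 10.** 1,000 simulated trials of 92 per setting; SD 16.9; linear-regression imputation, ANCOVA and Rubin pooling. Assumptions not in the documents: correlations of baseline with week 12 of 0.45, baseline with week 6 of 0.5, and week 6 with week 12 of 0.7 unless stated; week-6 effect 6 points; sex and age unrelated to outcome. Monte Carlo error is about 0.11.

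| Loss pattern | Loss by arm | Stated model, 5 data sets | Directly observed week-6 measure added, 5 data sets |
|---|---|---|---|
| Completely random | 15% / 15% | -0.03 | -0.05 |
| Poor responders leave, same in both arms | 16% / 15% | -0.09 | -0.03 |
| Poor responders leave, unequal rates | 6% / 24% | +1.38 | +0.11 |
| Opposite mechanisms by arm | 16% / 16% | +2.18 | -0.04 |
| Response-driven in one arm only | 10% / 28% | +2.61 | +0.06 |
| Same, week-6/week-12 correlation 0.5 | 10% / 27% | +1.36 | -0.10 |

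With 50 data sets and the stated predictors, the last four biases are +1.37, +2.18, +2.56 and +1.35. More data sets alone do not help.

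**3. Comparison with complete cases, no true effect.** 2,000 trials per setting; 5% random loss in one arm and about 26% response-driven loss in the other; baseline correlation 0.4.

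| Week-6/week-12 correlation | Complete-case bias | Stated model, 5 data sets | Type I error, stated model |
|---|---|---|---|
| 0.5 | 1.74 | 1.76 | 6.8% |
| 0.6 | 2.14 | 2.14 | 8.6% |
| 0.7 | 2.68 | 2.70 | 11.4% |

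The stated imputation and the complete-case ANCOVA agree to within 0.02 points. Across steps 2 and 3 the bias in the affected settings runs from about 1.4 to 2.7 points, or 14-27% of the 10-point difference.

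**4. What realistic auxiliaries achieve.** The near-zero column in step 2 requires the added variable to be the driver of dropout itself and to be observed for everyone. With one proxy correlated 0.7 with that driver, bias of 2.2-2.5 fell to about 1.3-1.7; with four such proxies it fell to about 0.7. If half the dropouts also lack week 6, the residual bias was 0.7 with a perfect measure and 1.7 with a proxy.

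**5. Too many auxiliaries.** At 20% loss, completers per arm are 46 × 0.8 = 36.8, about 37. With about ten auxiliaries imputed separately by arm, power was 73% against 73-75% for the plan. Under loss that differed by arm, the SD of the estimate was 4.0 against 3.6. Another run of the ten-auxiliary model gave 67% against 71%, and 72% against 77% in a second setting.

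**6. Five data sets.** The variance factor relative to infinitely many imputations is 1 + FMI/m, where FMI is the fraction of missing information and m the number of data sets. At FMI 0.10-0.20 and m = 5 it is 1.02-1.04, so the SE rises by 1-2%. The unadjusted SE is 16.9 × √(2/46) = 3.52. Imputation noise is 3.52 × √(FMI/m): 0.50-0.70 points with m = 5 and 0.16-0.22 with m = 50.

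**The case against.** The strongest reply is that the harm is conditional. The documents give no dropout rate, and difficulty adhering to exercise is not the same as leaving the trial. With equal rates and the same mechanism in both arms, the stated model showed no bias. This stands, so the size can only be given as a range under stated assumptions.

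The benefit can also be overstated. A reader might infer that adding week 6 data would remove the bias. The article schedules the VISA-A at baseline and week 12 only, and week 6 is a postal questionnaire that people who are leaving may not return. Proxies reduce the bias without eliminating it, and a large by-arm model can cost precision.

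Three other readings go further than the text.

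- The abstract says "Outcome measures will be obtained at baseline, 2, 6 and 12 weeks", which a reader might take to contradict Outcome measures. It is a collective sentence. Ultrasound and the heel rise test are not taken at every visit either, the Outcome measures text is explicit, and the figure with the schedule is not shown.
- The phrase "Multiple imputation will be used to replace any missing data using five iterations" might be read as confusing iterations with imputed data sets. It is only ambiguous, and five data sets is the natural reading.
- The stated imputation is not exactly a complete-case ANCOVA. Sex and age are extra, and the baseline scores may cover several measures. Near-equivalence is as far as the claim goes.

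None of this removes the core point: the predictor list is specified, and it omits data already being collected.

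**Conclusion.** The point holds in a limited form. The stated model gives results almost identical to a complete-case ANCOVA, so it cannot carry the role that the Sample size section gives it. If loss depends on early response and differs by arm in rate or mechanism, the primary comparison is biased by about 1.4 to 2.7 points, in favour of the arm that loses more of its poor responders. That range rests on an assumed 15-28% loss in the affected arm and week-6/week-12 correlations of 0.5-0.7. The bias is about zero if loss is the same in both arms. The documents do not show that such loss will occur, so it would be wrong to say that the primary result will be biased. The number of imputed data sets is a minor matter. This is a cheap improvement worth making before analysis.

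**What to change.** - Add a small, pre-specified set of post-baseline auxiliaries to the imputation model. One choice is pain VAS at weeks 2 and 6 plus one or two of week-6 PGIC, EQ-5D and adherence. Include the VISA-A at those visits only if it is in fact collected then.
- Keep group as a predictor. Do not impute separately by arm with every measure, because about 37 completers per arm cannot support it.
- State that variables excluded from data substitution, such as PGIC (read here as the self-reported symptom change), may still serve as predictors, and how their own missing values are handled.
- State the number of imputed data sets separately from the number of iterations, and use at least 20-50 data sets.

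The cost is a wording change, slightly more modelling and a little computing. No new data are needed. The expected return is less bias, by an amount that depends on how well the auxiliaries track dropout, and a modest power gain at best. The risk is some loss of precision if too many auxiliaries are used.
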